### Additional aims

Additional aims corresponding to hypotheses 4-8 above will be assessed.

## Main endpoints

### Primary endpoint:

1. Diagnosed ISUP grade  $\geq 2$  cancers

### Key secondary endpoints

2. Diagnosed ISUP grade 1 cancers
3. Performed biopsies
4. Performed MRI examinations

## Additional endpoints

The primary and secondary endpoints are reported in the tables below. All these endpoints can be used for comparisons between the nine diagnostic strategies listed in the 'Design' section.

## Study variables

### Primary endpoints

| Variable                               | Measure | Comment       |
|----------------------------------------|---------|---------------|
| Clinically significant prostate cancer | Yes/No  | ISUP $\geq 2$ |

### Key secondary endpoints

| Variable                                   | Measure | Comment                        |
|--------------------------------------------|---------|--------------------------------|
| Non-clinically significant prostate cancer | Yes/No  | ISUP = 1                       |
| Biopsy performed                           | Yes/No  | Any biopsy procedure performed |
| MRI performed                              | Yes/No  | MR procedure performed         |

### Other secondary endpoints

| Variable                      | Measure | Comment                  |
|-------------------------------|---------|--------------------------|
| Any cancerous finding         | Yes/No  | ISUP $\geq 1$            |
| ISUP $\geq 3$ prostate cancer | Yes/No  | ISUP $\geq 3$            |
| ISUP 2 through 5              | Yes/No  | Four separate endpoints: |

|                                        |         |                                                                                                                                                                                             |
|----------------------------------------|---------|---------------------------------------------------------------------------------------------------------------------------------------------------------------------------------------------|
|                                        |         | (1) ISUP=2, (2) ISUP=3, (3) ISUP=4, and (4) ISUP=5                                                                                                                                          |
| Lesion volume                          | ml      | Ellipsoid calc $(4 \times \pi \times h \times w \times l / 3)$
Total volume of all reported lesions
PIRADS $\geq 3$                                                                   |
| Number of biopsies                     | Integer | No of reported biopsy needles                                                                                                                                                               |
| Cancer length                          | mm      | total mm of cancer in reported biopsy                                                                                                                                                       |
| % Gleason $\geq 4$                     | %       | summarized % Gleason $\geq 4$ in needles with cancer                                                                                                                                        |
| Maximum cancer core length             | mm      | maximum length of cancer in any core                                                                                                                                                        |
| Maximum GS $\geq 4$ cancer core length | mm      | maximum length of Gleason $\geq 4$ cancer in any core                                                                                                                                       |
| Serious adverse events                 | Yes/No  | (1) Hospitalisation within 30 days after biopsy procedure, (2) infection treated with antibiotics within 30 days after biopsy procedure, or (3) death within 30 days after biopsy procedure |

*Independent variables*

| Variable                          | Measure | Comment                                        |
|-----------------------------------|---------|------------------------------------------------|
| Age                               | Years   | At referral creation                           |
| Previous prostate biopsy          | Yes/No  | Patient self-reported                          |
| Family history of prostate cancer | Yes/No  | Any first degree relative with prostate cancer |
| PSA                               | ng/ml   | At blood test                                  |
| free PSA                          | ng/ml   | At blood test                                  |

|                       |                         |                       |
|-----------------------|-------------------------|-----------------------|
| Stockholm3 risk score | % risk of ISUP $\geq$ 2 | At blood test         |
| prostate volume       | ml                      | MRI defined           |
| PI-RADS               | 1–5 (integer)           | Maximum PI-RADS score |

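### The SAP's lesion-volume formula is correct only for semi-axes; with full height, width and length it overstates every volume eightfold

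*Combined protocol and SAP*

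**What the plan says.** The SAP table headed "Other secondary endpoints" has a row for lesion volume, measured in ml. The comment column reads "Ellipsoid calc", followed by the expression 4 × π × h × w × l / 3. It then gives the quantity to be reported: "Total volume of all reported lesions" with PI-RADS 3 or higher.

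Neither the SAP nor the protocol defines h, w and l, calls them radii or semi-axes, says that measured dimensions are halved first, or gives their unit. The protocol's MRI sections (13.4) and the definition of a complete MRI in the protocol addendum set no convention for measuring lesions. Prostate volume, in the SAP's table of independent variables, is described only as defined by MRI. It therefore offers no second formula from which the convention could be inferred.

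**The concern.** The constant 4π/3 belongs with semi-axes, which are usually written a, b, c or r. The letters h, w and l suggest height, width and length, which are full extents. Pairing the semi-axis constant with full extents is a slip that a programmer following the table literally would carry into the data.

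What is at stake is the absolute value. The endpoint is declared in ml, so individual values, means, medians and standard deviations would all be inflated. The SAP (Additional endpoints) also allows the tabulated endpoints to be compared across the nine diagnostic strategies, so absolute differences in volume would be inflated by the same factor.

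**Working it through.** **Inputs**
- Formula: V = 4πhwl/3 (SAP, Other secondary endpoints). Coefficient 4π/3 = 4.189.
- Output unit: ml (same row). The input unit is not stated; cm is assumed here, since 1 cm³ = 1 ml. Measurements in mm would need division by 1000.
- Meaning of h, w and l: not stated. Both readings are worked through.

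The documents give no lesion-volume figure, so there is no stated result to reproduce.

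**Reading A: h, w and l are semi-axes.** The ellipsoid volume with semi-axes a, b, c is (4/3)πabc. The SAP formula is then right, and the ratio to the true volume is 1.

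**Reading B: h, w and l are full dimensions.** Then a = h/2, b = w/2 and c = l/2, so

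V = (4/3)π × (h/2)(w/2)(l/2) = πhwl/6, coefficient 0.5236.

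Ratio of the SAP formula to the true volume = (4π/3) / (π/6) = 8, whatever the size or shape of the lesion.

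| Lesion (cm, full dimensions) | SAP formula (ml) | πhwl/6 (ml) | Ratio |
|---|---|---|---|
| 0.5 × 0.5 × 0.5 | 0.524 | 0.065 | 8 |
| 1.0 × 1.0 × 1.0 | 4.189 | 0.524 | 8 |
| 1.0 × 0.8 × 1.2 | 4.021 | 0.503 | 8 |
| 1.5 × 1.0 × 2.0 | 12.566 | 1.571 | 8 |

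A Monte Carlo estimate of the 1.0 × 0.8 × 1.2 cm ellipsoid gave 0.503 ml, in agreement with πhwl/6.

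**Plausibility check.** The box that encloses the lesion has volume h × w × l. Under Reading B the SAP formula gives 4.19 times that box, and an ellipsoid cannot be larger than the box around it. The correct share is π/6, about 52%.

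**What the factor does downstream.** The endpoint is a sum over lesions, so a common factor of 8 carries through to each man's total. Means, medians, standard deviations and absolute differences are multiplied by 8. Ratios of volumes, rank orders, rank tests and standardised differences do not change.

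**The case against.** The strongest reply is that the decisive premise is not in the documents. The letters are undefined, the row is labelled as an ellipsoid calculation, and the expression is exactly right for semi-axes. A reader might infer that the SAP is proven to give wrong volumes, or that the trial's volumes are in fact wrong. The documents support neither statement. They show no derivation code and no reported volume, and Reading A cannot be excluded.

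A second reply concerns consequence, and it also stands. A reader might infer that an eightfold error disturbs a threshold or the trial's diagnostic conclusions. No lesion-volume threshold appears anywhere. The SAP names no test, power calculation, subgroup or imputation step that uses lesion volume, and its analysis text for secondary endpoints covers only serious adverse events. In the protocol (13.4), biopsy follows from the PI-RADS score, image quality and the Stockholm3 risk, not from a calculated volume. Nor do the documents contain an outside lesion volume against which a loss of comparability could be shown.

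What does not stand is the step from undefined symbols to no problem. Full extents are the ordinary meaning of h, w and l, and nothing says that they are halved. The protocol itself (8.5) speaks of tumour size in terms of diameter. Followed on its ordinary reading, the rule returns an impossible volume. The gap therefore lies in a stated formula and is more than missing detail.

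**Conclusion.** The point holds in conditional form. If h, w and l are full lesion height, width and length, which is their ordinary reading, the rule overstates every absolute lesion volume by exactly 8. If they are semi-axes, the formula is correct and only a definition is missing. In both cases the row needs a change. The size of the error rests on geometry alone; the only assumption is what the three letters mean. That the conditional statement is true is certain; that an error exists in the derived data is likely on the wording but not established.

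The effect is confined to absolute volumes in ml for one of the other secondary endpoints. Detection of ISUP grade 2 or higher, ISUP grade 1, biopsies performed and MRI examinations performed are all unaffected.

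**What to change.** Replace the expression in the lesion-volume row with π × h × w × l / 6, and define h, w and l as the full lesion diameters in cm, so that the result is in ml. If the recorded values really are half-diameters, keep 4π/3 and state that in the row. Then check the derivation code, and the unit in which dimensions were entered, before any volume is reported. If volumes have already been derived from full diameters with the present formula, dividing them by 8 corrects them.

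The cost is one line in the SAP and one line of code. No new data are needed, and no other analysis changes. The SAP's preface allows updates up to database lock. If the lock has already passed, the correction can be recorded as a dated clarification.

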## Additional hypotheses

1. When compared with performing systematic biopsies for men with elevated risk of prostate cancer in prostate cancer screening, targeted and systematic prostate biopsies performed on MRI positive men has non-inferior sensitivity for detecting clinically significant cancer (ISUP grade group  $\geq 2$ ) and reduces the number of performed biopsy procedures, which also translates to lower proportion of men with elevated risk who experience severe post-biopsy infections. Elevated risk can here be defined using PSA or S3M – we clarify the exact contrasts for testing this hypothesis below.
2. When compared with performing systematic biopsies for men with elevated risk of prostate cancer in prostate cancer screening, targeted biopsies only performed on MRI positive men has non-inferior sensitivity for detecting clinically significant cancer (ISUP grade group  $\geq 2$ ) and reduces the number of performed biopsy procedures, which also translates to lower proportion of men with elevated risk who experience severe post-biopsy infections. Elevated risk can here be defined using PSA or S3M – we will clarify the exact contrasts for testing this hypothesis below.
3. A diagnostic chain consisting of Stockholm3 followed by MRI and targeted+systematic biopsies (S3M+MRI+TBx+SBx) versus a diagnostic chain based on PSA  $\geq 3$  ng/ml followed by MRI and targeted+systematic biopsies (PSA+MRI+TBx+SBx) will lead to: non-inferior sensitivity for detecting clinically significant cancer (ISUP grade group  $\geq 2$ ); an inferior sensitivity for ISUP1 cancers (i.e. reduced overdiagnosis); and a reduction in the number of MRI examinations and performed biopsies.
4. A diagnostic pathway using the Stockholm3 test to select men for further workup using MRI followed by ONLY targeted biopsies (S3M+MRI+TBx) has non-inferior sensitivity for detecting clinically significant cancer (ISUP grade group  $\geq 2$ ) and reduces the number of performed biopsy procedures compared with a diagnostic pathway using systematic biopsies in men with PSA  $\geq 3$  ng/mL (PSA+SBx).
5. Biopsy compliance is higher after biopsy is recommended based on MRI compared to recommended without MRI.
6. SBx in the MRI arm has superior sensitivity than SBx in the non-MRI arm (due to cognitive fusion).

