### Key secondary aims

1. To test whether targeted prostate and systematic biopsies performed in MRI positive men will lead to: non-inferior sensitivity for detecting clinically significant cancer (ISUP grade group  $\geq 2$ ); reduced number of performed biopsy procedures; and lower proportion of men with elevated risk who experience severe post-biopsy infections compared to systematic biopsies for men with elevated risk (defined as being positive on PSA and/or Stockholm3) of prostate cancer in prostate cancer screening.
2. To test whether targeted prostate biopsies performed in MRI positive men will lead to: non-inferior sensitivity for detecting clinically significant cancer (ISUP grade  $\geq 2$ ); reduced number of performed biopsy procedures; and lower proportion of men with elevated risk who experience severe post-biopsy infections compared to systematic biopsies for men with elevated risk (defined as being positive on PSA and/or Stockholm3) of prostate cancer in prostate cancer screening.
3. To test whether a diagnostic chain consisting of Stockholm3 followed by MRI and targeted+systematic biopsies versus a diagnostic chain based on PSA  $\geq 3$  ng/ml followed by MRI and targeted+systematic biopsies will lead to: non-inferior sensitivity for detecting clinically significant cancer (ISUP grade group  $\geq 2$ ); an inferior sensitivity for ISUP1 cancers (i.e. reduced overdiagnosis); and a reduction in the number of MRI examinations and performed biopsies.
4. To test whether a diagnostic pathway using the Stockholm3 test to select men for further workup using MRI followed by ONLY targeted biopsies (S3M+MRI+TBx) has non-inferior sensitivity for detecting clinically significant cancer (ISUP grade  $\geq 2$ ) and reduces the number of performed biopsy procedures compared with a diagnostic pathway using systematic biopsies in men with PSA  $\geq 3$  ng/mL (PSA+SBx).

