## Statistical analysis

All analyses will be performed after the study is completed and the database is released. All statistics, including tables, figures and listings, will be performed using R version >3.5. Men creating referral before 2020-01-09 are included in main analysis. All participants with will be followed a minimum of 200 days after receiving the result from their blood sample (PSA and Stockholm3 score). In addition, biopsied men will be followed at least 30 days post-biopsy to monitor adverse events, and participants undergoing radical prostatectomy prior to database lock will be followed until pathology results from the prostatectomy are available.

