### Secondary endpoints

We will report the proportion of men with post-biopsy SAEs (see table “Secondary endpoints”) by study arm, where applicable.

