| 0.020 | 0.61 | 0.67 |
| 0.025 | 0.61 | 0.77 |
| 0.030 | 0.61 | 0.84 |
| 0.015 | 0.63 | 0.59 |
| 0.020 | 0.63 | 0.71 |
| 0.025 | 0.63 | 0.80 |
| 0.030 | 0.63 | 0.87 |

2. More than 90% power for the contrast PSA+MRI+TBx+SBx vs PSA+SBx (rDP = 1.3, noninferiority margin for  $\Delta DP \delta = 0.04$ ,  $\alpha = 0.025$ ).

Thus, contrast 1 drives the required samples size of the study. We therefore powered the study (with respect to sample size for sending out invitations and enrolling participants) to have sufficient statistical power to answer comparisons of Stockholm3 vs. PSA within the experimental arm.

Note: no correction for multiple comparisons was made. This means that each of the three tests (with respect to the ISUP 2, ISUP 1, and biopsy endpoints) has an approximate type I error rate of 2.5% if the corresponding null hypothesis is true. If all three null hypotheses are true and we assume the tests to be independent, the overall type I error rate is approximately 7%. In reality however, these hypotheses are strongly correlated. Thus, the overall type I error rate is bounded below by 2.5% and above by 7%.

R code for the power calculations is available at:

<https://gist.github.com/anddis/fc1a265d102b509b0eacd59ab065661a>

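### Key secondary aims 1 and 2 promise a test of severe post-biopsy infection, but the SAP defines only an unqualified adverse-event composite, reported descriptively with no stated denominator

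*Combined protocol and SAP*

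**What the plan says.** **The aim.** SAP, Key secondary aims 1 and 2, are worded as aims to test. One of the things to be tested is a "lower proportion of men with elevated risk who experience severe post-biopsy infections", with elevated risk defined as positive on PSA and/or Stockholm3. Hypotheses 1 and 2 give the mechanism: the MRI pathway "reduces the number of performed biopsy procedures, which also translates to lower proportion of men with elevated risk" with such infections.

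**The variable.** SAP, Other secondary endpoints, has one row for adverse events. It is headed Serious adverse events, is scored yes/no, and reads "1) Hospitalisation within 30 days after biopsy procedure, (2) infection treated with antibiotics within 30 days after biopsy procedure", with death in the same window as the third component. Neither this row nor any other variable defines severe infection.

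**The analysis.** SAP, Secondary endpoints, states: "We will report the proportion of men with post-biopsy SAEs", by study arm, where applicable. It names no denominator, margin or alpha. The multiplicity note in the sample size section refers to "each of the three tests (with respect to the ISUP 2, ISUP 1, and biopsy endpoints"; adverse events are not among them.

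**Who is observed.** SAP, Statistical analysis: "biopsied men will be followed at least 30 days post-biopsy to monitor adverse events". No corresponding adverse-event window is given for men who are not biopsied. Protocol 13.7 describes monitoring up to 30 days after biopsy, but the record check meant to deliver it looks for hospitalisation within 1 week.

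**The concern.** The aim and the variable do not match. As worded, the composite scores an antibiotic course for a mild infection, or an admission for an unrelated reason, the same as an admission for sepsis. Followed literally, the plan gives a figure that does not answer the infection part of aims 1 and 2.

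There is a second, conditional problem. The window opens at biopsy, so a man spared biopsy cannot have an event. For infections caused by biopsy that is correct, because he was spared the risk. For unrelated admissions, infections and deaths it is an artefact: those events occur in unbiopsied men too, but are not counted. With all randomised men as denominator, the arm with fewer biopsies would show a lower composite even if biopsy caused no harm. The result could then be cited in support of hypotheses 1 and 2.

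**Working it through.** **Inputs from the documents**
- About 2100 randomised (SAP, Updated sample size calculations). Check: 50000 x 0.25 = 12500; 12500 x 0.165 = 2063, which agrees.
- 2:3 allocation (SAP, Design): 2100 x 0.4 = 840 control and 2100 x 0.6 = 1260 experimental.
- 55% MRI-negative and 20% not following protocol (Protocol Addendum, sample size entry).
- Severe infection in 1-2% of biopsies (Protocol 8.3).

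The documents give no event rate, power or sample size for the adverse-event variable, so there is no stated figure to reproduce for it.

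**Assumption not in the documents:** unrelated countable events occur in b = 0.5-2% of men over 30 days.

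**Biopsied shares.** Two scenarios are used:
- 100% vs 45%. This is close to the SAP's PP population, which drops unbiopsied control men but keeps unbiopsied experimental men with PI-RADS <3 and Stockholm3 <25%.
- 80% vs 36% (0.8 x 45%), for ITT with 20% non-adherence in each arm.

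Both leave out MRI-negative men biopsied because Stockholm3 is at least 25%; their share is not given. Raising the experimental share from 45% to 55% of adherent men gives 80% vs 44%, shown as a third case.

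**Spurious difference when biopsy causes no harm, all randomised men as denominator:** b x (control share - experimental share).

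| b | 100% vs 45% | 80% vs 36% | 80% vs 44% |
|---|---|---|---|
| 0.5% | 0.275 points | 0.22 | 0.18 |
| 1% | 0.55 | 0.44 | 0.36 |
| 2% | 1.10 | 0.88 | 0.72 |

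The ratio of proportions is 0.45 in the first two columns and 0.55 in the third, whatever b is.

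**Comparison with the target.** The intended effect on severe infection at 100% vs 45% is 1% x 0.55 = 0.55 points to 2% x 0.55 = 1.10 points. The artefact equals it wherever b equals the severe-infection rate.

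**If the composite were tested** (the SAP does not plan this), with a Wald test at one-sided 0.025. At b = 1% and 100% vs 45%: SE = sqrt(0.01 x 0.99/840 + 0.0045 x 0.9955/1260) = 0.00392; 0.0055/0.00392 - 1.96 = -0.56; rejection rate about 29%. For b = 0.5%, 1% and 2% the rates are 17%, 29% and 51%, or 14%, 24% and 43% with 80% vs 36%. With one common 30-day window for every randomised man, the expected difference is 0 and the rate is 2.5%.

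**Dilution.** At 1% severe infection per biopsy, its share of the composite is 1/(1 + b), with b in percent: 67% at b = 0.5%, 50% at 1%, 33% at 2%.

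**Power for severe infection alone, 100% vs 45%.** At 1% per biopsy, about 8.4 vs 5.7 events and 29% power; at 2%, about 16.8 vs 11.3 events and 51% power. With 80% vs 36%, 24% and 43%.

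**Per biopsied man**, the unrelated rate is b in both arms and the artefact is zero.

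**The case against.** A reader might infer that the endpoint favours the MRI arm by construction. The documents do not support that as a general statement. The hypotheses say openly that fewer biopsies should mean fewer infections, so that part of any difference is the effect under study. Only biopsy-unrelated events are artefactual, and only with all randomised men as denominator. The SAP's reporting sentence names no denominator. Aims 1 and 2 do refer to men with elevated risk, and the SAP says analyses are reported on ITT and PP, so the all-randomised reading is the natural one, but it is not stated for this variable.

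A reader might also infer that the trial cannot examine severe infection at all. That goes too far. The three components are numbered separately, and hospitalisation for infection could be derived if the reason for admission is recorded.

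Further points stand against overstatement. That any cause counts is read from a missing qualifier; the text does not say it. The Protocol's follow-up section links the 30 days to post-biopsy infections. The SAP plans only descriptive reporting, so the rejection rates above describe a test nobody has specified. The background rate is assumed. The variable is listed among other secondary endpoints.

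None of this supplies a definition of severe infection, or the test that aims 1 and 2 announce.

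**Conclusion.** The mismatch holds on the text alone: aims 1 and 2 promise a test of severe post-biopsy infection, while the SAP provides an unqualified composite, reported descriptively with no stated denominator. The composite does not measure the aim's endpoint.

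The size of the artefact is conditional. It requires all randomised men as denominator and an unrelated rate that the documents do not give. Over an assumed 0.5-2%, it is about 0.3-1.1 points with 100% vs 45% biopsied and 0.2-0.9 points with 80% vs 36%, against an intended effect of 0.55-1.10 points under the first pair. It vanishes per biopsied man. The matter bears on the infection part of hypotheses 1 and 2; the ISUP, biopsy and MRI endpoints, and the primary conclusion, are not affected.

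**What to change.** 1. For aims 1 and 2, define severe post-biopsy infection by cause and severity, for example hospitalisation for infection within 30 days of biopsy.
2. Analyse it by arm with all randomised men as denominator, and show the rate per biopsied man alongside. This definition shrinks the artefact but does not fully remove it, since an unrelated infectious admission would still count only after a biopsy; the per-biopsied-man rate helps the reader judge that.
3. Report the three components of the composite separately, and do not use the unrestricted composite to support the infection part of hypotheses 1 and 2.
4. Either specify a test or label the result descriptive estimation with confidence intervals. Power of about 29-51% at best argues for saying plainly which it is.
5. If an all-cause comparison between arms is wanted, use one common window for every randomised man.
6. Reconcile the 1-week hospitalisation check in Protocol 13.7 with the 30-day window there and in the SAP. As described, that check would not capture an admission on days 8 to 30.

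The cost is SAP wording plus coding the reason for admission. The record review described is limited to hospitalisation within 1 week, in systems covering most but not all of the region's hospitals, so the coding may need more record work than is now planned. The narrower endpoint will have fewer events and less precision.
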